The Guideline-Informed Treatment for Personality Disorders (GIT-PD) offers an evidence-informed treatment framework, comparable to GPM and SCM. GIT-PD was developed in the Netherlands to enhance access to mental health care for individuals with PDs [31]. Hutsebaut et al. [31] describe GIT-PD as a principle-driven model designed to optimise common factors and effective treatment components, in a structured manner across four levels of implementation: The institution, the clinical pathway, the treatment team, and the individual therapist. Moreover, GIT-PD offers flexibility, allowing it to adapt to the specific clinical needs of individuals with PDs and the existing competencies of professionals. Compared to specialist treatments for PDs, GIT-PD is characterised by lower treatment intensity, shorter duration, reduced training and supervision requirements, and a less specialised therapist profile—all of which are expected to result in lower overall costs. A recent multicentre open cohort study based on routine outcome monitoring (ROM) demonstrated the feasibility of GIT-PD and suggested effect sizes comparable to those of most specialist treatments for PDs [32]. Lacking a control group and randomisation, the extent to which these findings are subject to bias and confounding remains unclear, warranting confirmation in a randomised controlled trial.

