### Sample size {19}

The required sample size was determined using a computer simulation. Twenty-one thousand datasets with varying sample sizes were simulated for an RCT design with seven repeated measurements on a continuous outcome variable, where both interventions exhibit equal improvement over time. The outcome measures were assumed to follow a multivariate normal distribution in both groups, with a repeated measures correlation of 0.50 and a decrease of *d* = 0.30 in both groups across the seven repeated measurements. Each of these datasets was analysed using a longitudinal multilevel model (see *Statistical methods for primary and secondary outcomes, including harms {27a}).* Subsequently, in each dataset, it was tested whether generalist treatment is non-inferior to specialist treatment by examining whether the lower limit of the two-sided 95% confidence interval of the difference between treatments in improvement over time is greater than the non-inferiority limit of *d* = 0.25. It was found that with this design, 316 participants are necessary (158 per group) to test non-inferiority with a power of 0.80 and α = 0.025. To account for attrition, which we estimate at 11.7% for the primary endpoint (T4) based on a similar study [19], the complete sample needs to consist of (316/0.883 = 357.87) 358 participants. This comes down to 179 participants per treatment condition.

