For both the CEA and CUA, the incremental costs (electronic patient file data and TiC-P) and the incremental effects (change in LPF as measured with the LPFS-BF-2.0 and STiP-5.1 for the CEA; QALYs as measured with the EQ-5D-5 L for the CUA) will be used to calculate incremental cost-effectiveness ratios (ICER). The uncertainty and robustness of the ICER will be analysed using bootstrapping. Next, the bootstrapped ICER will be plotted on cost-effectiveness planes where the horizontal axis displays the difference in effectiveness and the vertical axis displays the difference in costs. Further, the ICER will be used to examine willingness-to-pay (WTP) levels and then will be plotted in cost-effectiveness acceptability curves, displaying the cost-effectiveness of the experimental condition compared to the active control condition. Hence, WTP analysis will be conducted to determine the incremental costs per incremental unit of effect (QALYs or change in LPF) gained compared to WTP thresholds. A fitting discount rate will be applied for outcomes and future costs in accordance with NICE guidelines [123] and Drummond et al. [118]. Uncertainty in results will be assessed using both bootstrapping and sensitivity analyses. Variability and heterogeneity analyses will be conducted. Potential subgroups based on patient characteristics will be part of exploratory analyses.

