## Discussion

Although generalist treatments are widely used, the P-DAET trial is the first RCT assessing the non-inferiority of generalist treatment (GIT-PD) compared to specialist treatment (ST/MBT). We expect to find that, on average, generalist treatment is non-inferior to specialist treatment in terms of improving the level of personality functioning, general symptom severity and psychosocial functioning at post-treatment (18 months), as well as maintaining improvements at follow-up (30 months). Additionally, generalist treatment is expected to be more cost-effective than specialist treatment at both post-treatment and follow-up. Lastly, it is hypothesised that a combination of individual participant characteristics can predict differential treatment response above chance level, enabling the construction of a personalised treatment selection algorithm. P-DAET is, ultimately, aiming to contribute to the organisation of accessible and optimal allocation of cost-effective evidence-based psychotherapeutic care for those suffering from severe personality disorders by addressing these gaps in our current knowledge. The core clinical relevance of this study is determining whether a well-structured generalist treatment can serve as a non-inferior alternative to specialist treatment on average, while identifying which patients in particular require specialist care.

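### The willingness-to-pay comparison rests on the ICER, and the plan does not say how to read that ratio if generalist treatment is cheaper and less effective, a result this design makes likely

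*Protocol article*

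**What the plan says.** In the protocol article, the cost-effectiveness part of {27a} computes an ICER from incremental costs and incremental effects. The effects are change in level of personality functioning (LPF) for the cost-effectiveness analysis and QALYs for the cost-utility analysis. The ratio is bootstrapped, and "the bootstrapped ICER will be plotted on cost-effectiveness planes where the horizontal axis displays the difference in effectiveness", with cost on the vertical axis. Then "the ICER will be used to examine willingness-to-pay (WTP) levels and then will be plotted in cost-effectiveness acceptability curves". The comparison with thresholds follows: "WTP analysis will be conducted to determine the incremental costs per incremental unit of effect (QALYs or change in LPF) gained compared to WTP thresholds". On uncertainty the text adds: "Uncertainty in results will be assessed using both bootstrapping and sensitivity analyses".

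Three other places describe the expected result. The sample size simulation in {19} is one "where both interventions exhibit equal improvement over time". The background {9a} lists the lower intensity, shorter duration and lighter training and staffing of GIT-PD, "all of which are expected to result in lower overall costs". The Discussion states that "generalist treatment is expected to be more cost-effective than specialist treatment at both post-treatment and follow-up". The objectives {10} tolerate an effect down to d = -0.25.

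**The concern.** Cost per unit of effect gained is a meaningful quantity when the new treatment is more effective. This trial is not built on that expectation. It expects roughly equal effect at lower cost, so the denominator of the ratio is centred near zero and the numerator is expected to be negative. Results will then tend to fall on either side of the border between two cost-saving quadrants: cheaper and slightly better, or cheaper and slightly worse. A non-inferiority design explicitly accepts the second.

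In the cheaper-and-worse quadrant the ICER is a saving per unit of health given up. Setting it against a threshold for cost per unit gained reverses the inference. The third secondary objective, whether generalist treatment is more cost-effective in terms of personality functioning, depends on how this comparison is read.

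**Working it through.** **1. The plan's own figures.** The only relevant numbers are in {19}: 158 per group, 316 in total, power 0.80, α = 0.025, attrition 11.7%. The total reproduces: 316/0.883 = 357.87, so 358. The economic section gives no cost, QALY or threshold figure to reproduce.

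**2. The reversal.** Let ΔE be the effect difference (generalist minus specialist, improvement positive), ΔC the cost difference and λ > 0 the willingness to pay per unit of effect. Incremental net monetary benefit is INMB = λ·ΔE − ΔC.

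- If ΔE > 0, then ΔC/ΔE < λ exactly when INMB > 0.
- If ΔE < 0, multiplying through by ΔE flips the inequality, so ΔC/ΔE < λ exactly when INMB < 0.

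This needs no assumption about the data. An illustration with assumed values, λ = €50,000 per QALY:

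| ΔE (QALY) | ΔC (€) | ICER (€ per QALY) | ICER below λ? | INMB (€) |
|---|---|---|---|---|
| +0.01 | −5,000 | −500,000 | yes | 500 + 5,000 = +5,500 |
| −0.01 | −5,000 | +500,000 | no | −500 + 5,000 = +4,500 |
| −0.20 | −5,000 | +25,000 | yes | −10,000 + 5,000 = −5,000 |
| +0.20 | +5,000 | +25,000 | yes | 10,000 − 5,000 = +5,000 |

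Rows 1 and 2 are almost the same result, yet their ratios lie at opposite extremes. Rows 3 and 4 have the same ratio and opposite net benefit.

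**3. How likely a negative effect estimate is.** Under the {19} assumption the true LPF difference is zero, so a symmetric estimate is negative with probability 0.50. At power 0.80 and margin 0.25, the implied standard error is 0.25/(1.960 + 0.842) = 0.089 SD. Non-inferiority is then shown when the estimate exceeds −0.25 + 1.960 × 0.089 = −0.075 SD. Every positive estimate passes, so:

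- non-inferior with a negative estimate: 0.80 − 0.50 = 0.30 of all trials;
- as a share of the trials that show non-inferiority: 0.30/0.80 = 37.5%.

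If costs are lower, as expected, each of these trials falls in the cheaper-and-worse quadrant for LPF.

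**4. What cannot be computed.** The frequency of a wrong economic conclusion depends on inputs that the article does not give. As an illustration only, cost and QALY differences were simulated as independent normal estimates with 158 per arm. Assumed inputs were QALY SD 0.25–0.35, cost SD €15,000–30,000 and thresholds of €20,000–80,000, with a true QALY difference of 0. The ratio was compared with λ regardless of the sign of ΔE:

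| Assumed saving (€) | ICER below λ | INMB above 0 |
|---|---|---|
| 5,000–10,000 | 50–62% | 86–100% |
| 2,000 | 55–76% | 67–87% |

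The gap between the two rules depends heavily on the assumed saving.

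**The case against.** The strongest reply is that the article never states a rule of the form: cost-effective if the ICER is below the threshold, whatever the sign of the effect difference. The threshold sentence speaks of effect gained, and it follows as a summary of the planned planes and curves. A single ratio cannot be plotted on a plane with separate effect and cost axes, so ICER is probably loose wording there for the bootstrapped cost-effect pair. If the acceptability curve is the share of pairs below the threshold line, it equals the bootstrap probability of positive net benefit and the reversal does not arise. The article also cites CHEERS and ISPOR guidance and condenses a fuller protocol, so the absence of the term net benefit is not in itself a fault.

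Most of this stands, and it rules out several stronger readings that a reader might infer:

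- *The plan commits to a sign-blind rule.* It does not say so.
- *The comparison is close to a coin toss, or wrong half the time.* That takes the sign-blind rule literally and uses assumed savings, SDs and thresholds. The equal-improvement assumption in {19} is not made for QALYs, and the expected saving is neither quantified nor stated for the societal costs used in {27a}.
- *A poor-value generalist treatment would almost always be endorsed.* This needs a clearly worse treatment. A loss of 0.15 QALY with an assumed SD of 0.2–0.4 is d = −0.375 to −0.75, which is 1.5 to 3 times the margin.
- *An invalid bootstrap interval for the ratio is planned.* No such interval is promised.
- *The direction of LPF is wrong.* Higher scores mean worse functioning on both instruments, but the plan defines the effect as improvement.

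The reply does not remove the stated comparison itself. It is expressed as a ratio against a threshold, the curves are described as drawn from that ratio, and neither statement covers a quadrant that the design is likely to reach.

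**Conclusion.** The concern holds as a poorly fixed analysis choice, not as proof that the economic analysis will be wrong. The reversal for a cheaper and less effective treatment is exact. For the LPF-based analysis, about half of the effect estimates would be negative under the plan's own assumption, and about 30% of trials would combine non-inferiority with a negative estimate. Those shares assume a symmetric estimate, a true difference of zero, the stated 80% power, and an economic LPF difference with the same sign as the trial's estimate. That these trials also fall in the cheaper-and-worse quadrant assumes that costs are in fact lower. No error rate for the final economic conclusion can be stated from the document. The change is worth making because a better-behaved statistic is available from the same bootstrap and the third secondary objective depends on the reading.

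**What to change.** In the cost-effectiveness part of {27a}:

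- Base the willingness-to-pay comparison on INMB = λ·ΔE − ΔC, with LPF improvement coded positive, and report it with a bootstrap 95% confidence interval over a stated range of λ for QALYs and for LPF.
- Define the acceptability curve as the share of bootstrap cost-effect pairs with INMB > 0 at each λ.
- Report the ICER descriptively, together with the share of pairs in each quadrant of the plane.

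This changes the analysis wording only. The bootstrap pairs are those already planned, and no extra data or participants are needed.

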##### Social problems list (IAPT)

Seventeen areas of social problems, such as unemployment and social isolation, are logged using yes/no items of the Social Problems list derived from the Improving Access to Psychological Therapies (IAPT) program [102]. An 18^th^ item provides the opportunity to log additional social problems not covered by the seventeen areas previously inquired. No prior psychometric validation has been executed.

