*Personalised Advantage Index*. In examining what treatment works better for whom, an algorithm will be built that predicts differential treatment responses regarding LPF between generalist and specialist treatment. The algorithm quantifies the magnitude by which either treatment is estimated to outperform the other on the participant level, using the Personalised Advantage Index (PAI). The PAI was initially developed by DeRubeis et al. [44], but recently Meinke et al. [124] revised the algorithm, addressing key analytical issues in the traditional approach. As a result, this Advanced PAI approach introduced less risk of bias and prevented data leakage, thus providing more precise estimates while minimising the risk of overestimating model performance. Following Meinke et al.’s [124] guidance, PAI analyses will be conducted using their open-source code. This means a 5-fold cross-validation with 100 iterations will be utilised, covering not only the data preprocessing steps in terms of candidate predictor exclusion, imputation, and selection but also training, testing, and evaluating the performance of the models. More specifically, candidate predictors will be excluded if more than 30% of values are missing, while imputing missing values for the remaining candidate predictors. Herein, the mode will be used for categorical and binary variables, while multivariate imputation by chained equations (MICE) is going to be used for numerical variables. Furthermore, predictors lacking variance and binary predictors with 90% of participants or more in either category will be excluded. Multicollinearity between candidate predictors is operationalised as Pearson correlation (numerical variables) or Jaccard similarity (binary variables) of  > 0.75. Either of two similar candidate predictors should be removed by excluding the variable with the highest mean correlation/similarity with the remaining predictors. Candidate predictor exclusion will be repeated until no correlation/similarity of  > 0.75 is observed.

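### The PAI collinearity filter for binary predictors uses Jaccard similarity, which depends on 0/1 coding and can delete an independent candidate moderator

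*Protocol article*

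**What the plan says.** The point lies in the Personalised Advantage Index paragraphs of Statistical methods {27a} in the protocol article.

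- **Measure and cut-off:** "Multicollinearity between candidate predictors is operationalised as Pearson correlation (numerical variables) or Jaccard similarity (binary variables", with a threshold of more than 0.75.
- **Which variable goes:** "Either of two similar candidate predictors should be removed by excluding the variable with the highest mean correlation/similarity with the remaining predictors".
- **Stopping rule:** "Candidate predictor exclusion will be repeated until no correlation/similarity of" more than 0.75 is left.
- **Prior exclusion of near-constant variables:** "predictors lacking variance and binary predictors with 90% of participants or more in either category will be excluded".
- **Implementation:** "PAI analyses will be conducted using their open-source code"; that code is not part of the document.
- **Where it runs:** inside the resampling loop, since "a 5-fold cross-validation with 100 iterations will be utilised" and this covers predictor exclusion as well as model fitting. Elastic Net selection and a final Ridge fit follow, separately for each treatment.

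Binary candidates exist. Seventeen areas of social problems "are logged using yes/no items of the Social Problems list", and several of the listed demographic characteristics may also be coded as binary. The text does not say which category of a binary variable is coded 1.

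**The concern.** A collinearity filter should remove a predictor when another already carries the same information. Jaccard similarity is the number of participants with both variables equal to 1, divided by the number with at least one equal to 1. It ignores participants with 0 on both. Two variables that are merely both frequent therefore score high without being associated, and two that are exact mirror images score zero. Swapping the 0/1 labels of both variables leaves the information unchanged but can move Jaccard across the threshold.

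At stake is the fourth secondary objective, which asks whether a combination of patient characteristics predicts differential response. The filter acts before Elastic Net. A moderator deleted there cannot be recovered by the later models, and the deletion could result from a labelling choice that the plan does not fix. A team that repeats the analysis with another coding could start from a different predictor set.

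**Working it through.** The plan reports no figure to reproduce here; 0.75 and 90% are design constants. The check works out what the rule does.

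**Inputs.** Jaccard threshold 0.75, and exclusion when 90% or more are in one category (both from {27a}). Planned N = 358 (Trial design {12}); 316 after the planned 11.7% attrition (Sample size {19}). An 80% training part is 0.8 × 358 ≈ 286, or 0.8 × 316 ≈ 253.

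**1. Independent binaries.** With coded-1 prevalences p and q, the expected joint proportion is pq, so J = pq/(p + q − pq). For p = q this is J = p/(2 − p).

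- Threshold for equal prevalences: p/(2 − p) = 0.75 gives 1.75p = 1.5, so p = 6/7 = 85.7%.
- Threshold with the partner at the 90% limit: 0.9p = 0.75(0.9 + 0.1p) gives 0.825p = 0.675, so p = 81.8%.
- Largest value under the 90% rule: just under 0.9/1.1 = 0.818.

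Independent pairs can thus be flagged when both prevalences lie at about 82–90%, or above 85.7% if they are equal.

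**2. The same pair under the other coding.**

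| Prevalence (both) | J | J after recoding both |
|---|---|---|
| 80% | 0.667 | 0.111 |
| 85% | 0.739 | 0.081 |
| 87% | 0.770 | 0.070 |
| 88% | 0.786 | 0.064 |
| 89% | 0.802 | 0.058 |

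For example, at 88%: 0.88/1.12 = 0.786; at 12%: 0.12/1.88 = 0.064. Phi is zero in every row under either coding.

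**3. Sampling.** This is the share of 20,000 simulated independent pairs with J > 0.75, among pairs where both variables pass the 90% rule.

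| Prevalence (both) | n = 286 | n = 253 |
|---|---|---|
| 80% | 0.001 | 0.003 |
| 84% | 0.16 | 0.17 |
| 85% | 0.33 | 0.34 |
| 86% | 0.55 | 0.53 |
| 87% | 0.76 | 0.73 |
| 88% | 0.90 | 0.88 |
| 89% | 0.97 | 0.95 |

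The choice between the two training sizes makes little difference.

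**4. Complementary variables.** For x and 1 − x nobody has 1 on both, so J = 0 although phi = −1. Both are kept.

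**5. What 0.75 means in terms of association.** For equal prevalence p, J = 0.75 requires a joint proportion of 0.75 × 2p/1.75, and phi = (joint − p²)/(p(1 − p)).

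- p = 15%: joint = 0.1286, phi = 0.83
- p = 50%: joint = 0.4286, phi = 0.71
- p = 85%: joint = 0.7286, phi = 0.05

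One printed threshold therefore demands near-duplication for rare categories and almost no association for frequent ones.

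**6. After the change.** With |phi| > 0.75, complementary pairs are flagged (1 > 0.75) and independent pairs are not (0), under either coding.

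**The case against.** The strongest reply concerns reach.

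- **Narrow band.** Both variables must have their coded-1 category at about 82–90%; at 80% a false flag is practically absent. No candidate is shown to lie there. For the social-problem list with yes coded 1, two items would each need endorsement at that level, and the text does not say whether the items enter singly or as a count. This stands.
- **Little information lost.** The models are fitted per arm. At 88% prevalence, the minority category in a training fold holds about 0.12 × 253/2 ≈ 15 to 0.12 × 286/2 ≈ 17 participants per arm. A moderator lost in this way would have been weakly estimated in any case. This also stands.
- **Published pipeline.** Following existing code has value, and under one fixed coding the outcome is a reproducible function of the data. That is true, but it does not make Jaccard a measure of redundancy.

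A reader might also infer that the numerical half of the filter is faulty: no absolute value is printed, so a pair at r = −0.9 would survive, and the mean used to choose the dropped variable would be signed. The documents do not establish this. A correlation above 0.75 is ordinary shorthand for its strength, and the cited code, which may take absolute values, is not at hand. The PAI text does write the word absolute elsewhere, for the PAI scores, but that is weak evidence. On this half, a clarification is all that can be asked.

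**Conclusion.** The Jaccard fault holds as algebra and does not depend on how the text is read. For binary candidates the rule can delete one of two independent predictors because of their coding (J = 0.786 at 88%, 0.064 at 12%), and it keeps exact complements. The main harm is the coding-dependent loss of a candidate moderator before selection.

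The size is small. The deletion result assumes independent predictors with both coded-1 prevalences at about 82–90%, and how many candidates meet that is unknown. Redundancy that slips through matters little, since Elastic Net and Ridge tolerate it. The PAI is an exploratory secondary objective; the non-inferiority tests and the economic evaluation are untouched.

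Two wider conclusions are not supported. Recoding does not always reverse the decision: with both prevalences at 50%, recoding both variables leaves Jaccard unchanged. Nor does the rule threaten frequent binary predictors in general, as the 80% row shows.

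**What to change.** In the Personalised Advantage Index part of {27a}:

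- replace Jaccard by |phi| > 0.75 for pairs of binary variables;
- write |Pearson r| > 0.75 for pairs of numerical variables, which is only a clarification if the cited code already takes absolute values;
- choose the variable to drop by its mean absolute association with the remaining predictors.

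This makes the filter independent of 0/1 coding and of scoring direction. The cost is one sentence in the plan, a small change to the script, and a short note recording the departure from the cited open-source code. According to Trial status, data collection runs to December 2029, so the change can be documented well before the PAI analysis.

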
#### Criteria for discontinuing or modifying allocated interventions {15b}

The sponsor will suspend the study if there is sufficient ground that continuation of the study will jeopardise participant health or safety. Suspension is deemed unlikely as this study only includes regular treatment programs that have already been implemented and sustained at these sites in the Dutch mental health care system. Therapeutic progress is evaluated throughout the allocated treatment. If the therapist deems it necessary to modify the treatment, push the participant out of the allocated treatment or cross the participant over to the alternative treatment arm, then this decision needs to be discussed with the therapist in the Trial Steering Committee. Furthermore, participants can decide to discontinue the allocated treatment if desired.

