Subsequently, distinct prediction models are to be fitted for the generalist and specialist treatment. First, predictors will be selected using Elastic Net regression, which is a supervised machine-learning method that combines the penalised linear Lasso and Ridge regressions to identify a parsimonious and stable subset of predictors. Then, Ridge regression will be used to fit the final prediction models using the selected predictors per treatment. For the participants in the test-fold of the 5-fold cross-validation, the resulting prediction models will be used to calculate a ‘factual’ prediction for the treatment actually received and a ‘counterfactual’ prediction for the treatment not actually received. To quantify the performance of the prediction models for both treatments, the outcome of the factual prediction will be compared to the actual LPF at post-treatment in terms of the mean absolute error (MAE), the root mean square error (RMSE), and the correlation.

The PAI scores are then derived from subtracting the counterfactual prediction from the factual prediction to discern whether a participant received their optimal or non-optimal treatment. Negative and positive PAI scores refer to having received the optimal and nonoptimal treatment, respectively. The PAIs utility in guiding treatment selection will be evaluated through comparing LPF at post-treatment for participants having received their optimal versus nonoptimal treatment using an independent one-sided t-test. Additionally, Cohen’s *d* will be computed for the mean difference. As per customary practice in PAI analyses, this evaluation should be repeated for the 50% of participants with the largest absolute PAI scores to determine utility for those with the strongest predictions. The Advanced PAI approach will be performed for both the clinician-rated (STiP-5.1) and the self-reported LPF (LPFS-BF 2.0).

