#### Definition of analysis population {27b}

Following the intention-to-treat principle, participants will be analysed according to the assigned intervention arm, disregarding actual compliance with the assigned intervention. Furthermore, in inspecting the robustness of the noninferiority outcomes, supportive sensitivity analyses are carried out per-protocol, meaning only participants who did not drop out of the assigned intervention are included.

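### The PAI text labels participants by treatment received although the analysis population is by assigned arm; applied literally, progress-related and mainly one-way crossover can make the PAI look useful without any moderation

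*Protocol article*

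**What the plan says.** The PAI part of the protocol article's statistical methods section {27a} fits one prediction model per treatment. For each test-fold participant it then produces "a ‘factual’ prediction for the treatment actually received and a ‘counterfactual’ prediction for the treatment not actually received". The counterfactual "prediction for the treatment not actually received" is subtracted from the factual one to give the PAI score, and its sign decides whether the participant counts as having had the optimal treatment. Utility is judged by "comparing LPF at post-treatment for participants having received their optimal versus nonoptimal treatment", "using an independent one-sided t-test", and the comparison is repeated in the half of participants with the largest absolute scores. The article also states that "a 5-fold cross-validation with 100 iterations will be utilised".

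The analysis-population section {27b} says that "participants will be analysed according to the assigned intervention arm, disregarding actual compliance with the assigned intervention". It names no exception for the PAI, and it ties the per-protocol runs to one purpose: "in inspecting the robustness of the noninferiority outcomes, supportive sensitivity analyses are carried out per-protocol". Within {27a}, the non-inferiority and economic paragraphs each state intention-to-treat; the PAI paragraphs do not.

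Three sections bear on whether received and assigned arm can differ:

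- {15b}: after noting that progress is evaluated throughout treatment, it provides that a therapist may judge it necessary to "push the participant out of the allocated treatment or cross the participant over to the alternative treatment arm", subject to discussion in the TSC.
- {15d}: participants may not receive the other condition's interventions while the trial lasts.
- {34}: institutions may not provide opposite-arm care unless the TSC gives permission. Participants who discontinue are still assessed and analysed by intention-to-treat.

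**The concern.** The factual/counterfactual contrast can be interpreted because the arm was randomised. If the arm label instead follows what a participant ended up receiving, anyone who crosses over moves into the other arm's model and may change between optimal and nonoptimal. When crossover depends on poor progress, the label depends on the outcome. If such crossover runs mainly one way, the arm that gains the poor progressers looks worse on average. The other arm is then called optimal for most participants, and the utility test compares groups that differ for that reason alone.

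A participant who never starts treatment also has no label under a literal reading.

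At stake is the fourth secondary objective: a false signal that patient characteristics can guide the allocation of scarce specialist places.

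**Working it through.** **The plan's own figure.** The article states no crossover rate and no operating characteristics for the PAI test. Its only related figure is the sample size. A linear change over seven equally spaced measures with correlation 0.50 has variance 0.5/0.778 = 0.643. Then n = 2 × (1.96 + 0.842)² × 0.643 / 0.25² = 161.5, so 162 per group and 324 in total, within 3% of the stated 316. For attrition, 316/0.883 = 357.87, which gives 358 as stated. The check below uses 316 evaluable participants, 158 per arm.

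**Size of the spurious arm difference.** Assume no true arm difference and an outcome SD of 1. Let q be the share of the generalist arm that crosses, chosen as the worst on a progress measure correlated ρ with the final score. Let φ(z) be the normal density at the upper-q point. The difference between received groups is

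ρφ(z)/(1 − q) + ρφ(z)/(1 + q) = 2ρφ(z)/(1 − q²).

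If 5% of all participants cross one way, q is about 0.10 (16/158) and φ(z) = 0.1755. The factor is 2 × 0.1755/0.99 = 0.354, giving 0.18 SD at ρ = 0.5 and 0.28 SD at ρ = 0.8.

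**Simulated PAI utility test.** Settings:

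- 316 participants, no treatment effect, no moderation.
- 20 standard-normal predictors, four of them prognostic (4 × 0.25² = 0.25 of outcome variance).
- Elastic Net selection followed by ridge regression in each arm, with fixed penalties.
- 5-fold cross-validation averaged over 4 repeats instead of 100, without the open-source code that the article cites.
- One-sided level 0.05, which is an assumption because the article states none for this test.
- 1,200 trials per scenario, so the Monte Carlo standard error is at most √(0.25/1200) = 1.4 percentage points.

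The table gives the share of trials in which the PAI is declared useful when participants are labelled by treatment received. Crossover is a share of all participants, and one-way means generalist to specialist.

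| Crossover | Direction | ρ | All participants | Half with largest absolute PAI |
|---|---|---|---|---|
| none | – | – | 8.7% | 6.7% |
| 2% | one-way | 0.5 | 11.2% | 10.3% |
| 5% | one-way | 0.5 | 22.3% | 23.0% |
| 5% | one-way | 0.8 | 54.8% | 51.5% |
| 10% | one-way | 0.5 | 53.6% | 47.5% |
| 10% | one-way | 0.8 | 93.6% | 89.9% |
| 5% | both ways | 0.5 | 9.5% | 9.5% |
| 10% | both ways | 0.5 | 8.4% | 9.0% |
| 5% | one-way | 0 | 9.3% | 9.7% |
| 10% | one-way | 0 | 11.7% | 12.0% |

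**Labelling by allocated arm.** In this set-up crossover does not alter outcomes and the allocated labels stay random, so the rate is 8.7% whatever the crossover.

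**Cross-check of the mechanism.** With no crossover, a true main effect of d = 0.2 and no moderation, the test rejects in 25.3% of trials. That is close to the 22.3% produced by the 0.18 SD artefact, as expected if the test is reacting to an average difference between the groups.

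**The case against.** The strongest reply is that treatment actually received is ordinary PAI language for the observed arm as against the hypothetical one. On that view the PAI text sets up no as-treated population, and the general rule in {27b} governs it. This may well be what the authors mean, and never-starters would then keep their assigned arm. What stands is that the PAI text does not say so, omits the intention-to-treat statement made for the other analyses, and literally points the other way.

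Second, crossover should be uncommon. {15d} prohibits it, and notes that Dutch insurance covers one personality disorder treatment at a time. {15b} requires TSC discussion. {34} requires TSC permission, and there the context is care after the allocated treatment is complete, when a participant has in fact received that treatment. {15b} also does not make poor progress the criterion for crossing over. All of this limits the likely size, but it leaves routes by which the labels can diverge.

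Third, the inflation depends on assumed conditions. {15b} applies to both arms, and the controls show little effect when crossover is two-way or unrelated to progress. This is correct and belongs in the conclusion. One-way step-up is plausible because the article describes generalist treatment as the less intensive option, but the article does not predict it.

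A reader might infer three stronger things that the documents do not support:

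- That the PAI is definitely scored as-treated. The text is ambiguous.
- That every PAI score is biased towards generalist treatment. This holds only under the stated crossover pattern.
- That the non-inferiority result is at risk. That analysis is explicitly intention-to-treat, so comparing the artefact with the margin of 0.25 has no bearing.

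**Conclusion.** The wording conflict between the PAI text in {27a} and the population rule in {27b} is real and should be removed. Its consequence is conditional. If labels follow treatment received, and crossover is both progress-related and mainly one-way, the utility test is positive without moderation in about 11% of trials at 2% crossover and in 22% to 55% at 5% (correlation 0.5 to 0.8), against about 9% with none. When either condition is absent, the rate is 8.4% to 11.7%. The crossover rates, direction and correlations are assumptions, and the simulation approximates the planned algorithm.

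The point concerns an exploratory secondary objective and leaves the primary conclusion untouched. Labelling by allocated arm removes this route to a false signal. It does not cure the test's mildly liberal baseline (8.7% at a nominal 5%) or its tendency to reject when there is a true main effect but no moderation (25.3% at d = 0.2).

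**What to change.** In the PAI text of {27a}, define the factual prediction by the treatment allocated by randomisation and the counterfactual prediction by the treatment not allocated. Fit both arm models and assign the optimal and nonoptimal labels by allocated arm, and state that this follows {27b}. Any run by treatment received should be a sensitivity analysis only.

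Separately, {15b}, {15d} and {34} should be reconciled so that they give one consistent account of whether and how crossover can occur. Which rule applies is for the trial team.

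The cost is a few words and no new data. The score then describes being offered a treatment rather than receiving it, which suits the stated aim of exploring treatment allocation.
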